## Trial design {8}

This study is a single-blinded, prospective randomized controlled trial with subjects randomized 1:1 in two parallel groups, i.e., experimental (L-PRF treatment) and active control (commercially available fibrin sealants).

In this study, the general objective is to show the non-inferiority of L-PRF as a closure technique compared to commercially available fibrin sealants in supra- and infratentorial surgery. This prospective randomized controlled trial was approved by the local Ethical Committee (UZ Leuven, S61460) and is registered at ClinicalTrials.gov (ID: NCT03812120) [2]. Recruitment started on 06 January 2020.

Demographic data, medical history, and surgical indications are reported prior to surgery. During the hospitalization (from 1 day preoperatively until the day of discharge), vital parameters such as body temperature and blood pressure are monitored, as well as medication intake. Patient’s quality of life (QoL) is questioned using the Research and Development 36-item Short Form Survey (RAND SF-36) and EuroQol Five Dimensions (EQ-5D) questionnaires.

To perform a cost-effectiveness evaluation, all costs and effects will be collected. Additionally, patient’s general quality of life is assessed using the EQ-5D-3L Questionnaire prior to surgery and at the 6–12 weeks follow-up visit (FU3). Complications and adverse events are assessed at the time of surgery, 2 days postop (FU1), at hospital discharge (FU2), and at follow-up visits (FU3) (Fig. 2).

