## Outcomes {12}

The primary endpoint is the success rate of both techniques, which means the absence of a clinically relevant CSF leak at 12 weeks after surgery, i.e., any leak that needs surgical revision or any other intervention, e.g., puncture or aspiration, longer hospitalization, or repeat imaging. The success rate in both groups will be reported in proportions with a 95% confidence interval.

Secondary endpoints include an analysis of peri- and postoperative complications (CSF leakage, both clinically relevant (incisional leakage) and not clinically relevant (swelling, pseudomeningocele), surgical site infection and treatment-site bleeding in particular), as well as a cost-effectiveness evaluation. In addition, the study will compare the efficiency of L-PRF in supratentorial and infratentorial surgery, based on surgical approach and technique.

Peri- and postoperative complications will be obtained from the hospital databases. Each complication requiring additional treatment (surgical revision, intervention, or drug therapy) or investigation (clinical or imaging) or which requires or prolongs hospitalization will be considered. RAND SF-36 questionnaires will be filled out preoperatively (baseline) and 6–12 weeks post-surgery to evaluate patient-reported health concepts such as physical functioning, bodily pain, role limitations due to physical health problems, role limitations due to personal or emotional problems, emotional well-being, social functioning, energy/fatigue, and general health perceptions. The questionnaire is scored as indicated on the official website of RAND, adapted from the scoring described by Ware and Sherbourne [10]. The difference in the change in score to baseline will be compared between the groups, i.e., treated with commercially available fibrin sealants or treated with L-PRF.

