For the cost-effectiveness analysis, the “healthcare payer” perspective will be adopted, which means that all direct treatment-related costs as well as costs related to follow-up will be included in the analysis. For the cost analysis, the following outcomes will be considered: used materials during surgery (units), surgery duration (minutes), intensive care hospitalization time (days/hours), duration of hospitalization (days), associated facility, and staff resources. These data will mainly be retrieved from the hospital records and requested at the hospital’s billing office, if necessary. The most recent unit prices at the time of analysis will be applied. Depending on the primary outcome, i.e., the effectiveness of dural closure, and the clinical effects of both treatments, analysis will be performed as cost-utility or as cost minimization [11, 12]. In addition, the use of EQ-5D-3L to calculate QALYs at 6–12 weeks postoperative will be explored to compare EQ-5D utility scores to other outcomes described above.

The outcomes will be assessed at five study visits within a timeframe of twelve postoperative weeks (Table 2), and a comparison will be made between the two groups considering the change to baseline. Data will be presented as mean and standard deviation or median and interquartile range for continuous variables (including body temperature, °C; blood pressure, mmHg; diameter of craniotomy, mm) and as proportions with 95% confidence intervals for categorical variables (complications, surgical indication, surgical approach). Baseline medical characteristics will be compared between the allocation groups in a similar fashion.

**Table 2 Tab2:** Outcome assessment

Procedure	Visit 1: *screening*	Visit 2: *allocation*	Visit 3: *FU1*^a^	Visit 4: *FU 2*^b^	Visit 5: *FU 3*^c^

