### Sample size {14}

Sample size calculation was performed according to the primary outcome, using an online power calculator for binary outcome non-inferiority trials (Sealed Envelope Ltd. available from: www.sealedenvelope.com). This is a non-inferiority trial with a binary outcome using a one-sided alpha of 0.05 and 80% power. The assumed success rate is 93.7% in the control arm, based on center-specific experience as well as the literature [13]. Data on the use of L-PRF for this indication is limited, but we assume a 95% success rate based on a prior feasibility study [9].

The statistical hypothesis for testing the treatment difference is presented as follows: H_0_: Δ ≤  − 0.05 tested against the alternative hypothesis and H_A_: Δ >  − 0.05, where Δ is the difference between the success rates of experimental and control condition and − 0.05 is the non-inferiority difference. The non-inferiority limit was set at 0.05 considering (1) reported CSF leakage rates without commercially available fibrin sealant averaging 17.2% [14] and (2) important additional benefits of L-PRF compared to commercially available fibrin sealants including the completely autologous nature (eliminating immune reactions), presence of immunologic cells and reduced costs.

Based on this power calculation, 334 patients need to be included, 167 in each group. A drop-out rate of 2–5% is expected due to loss of follow-up and non-adherence to the allocation or failure of L-PRF preparation. Therefore, 350 patients will be enrolled, 175 in each group.

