### Statistical methods

### Statistical methods for primary and secondary outcomes {20a}

Data will be analyzed in the GraphPad Prism software using a simple *t* test, or non-parametric Mann–Whitney *U* test when not normally distributed, with Bonferroni Holm correction for multiple testing. A *p*-value ˂ 0.05 is considered statistically significant. The primary outcome, i.e., CSF leakage, will be analyzed in terms of a difference in risk between the two treatment groups. The mean difference between the two treatment groups will be reported as a two-sided 95% confidence interval. Secondary endpoints will be calculated using a simple *t* test, non-parametric Mann–Whitney *U* test when not normally distributed, Fisher’s exact test, or chi-squared test, based on the number of events.

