### Methods for additional analyses (e.g., subgroup analyses) {20b}

Subgroup analyses will be performed for surgical indication (tumor, vascular or functional), craniotomy diameter (small: ˂ 30 mm; medium: ˃ 30 mm; ˂ 80 mm; and large: ˃ 80 mm) recurrent surgery, patient age, gender, medication use, and alcohol and smoking habits. The data will be statistically tested using a simple *t* test or Mann–Whitney *U* test, or Fisher’s exact test or chi-squared test depending on normality, type of variable, and number of events. We do not intend to perform adjusted analyses.

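### RAND SF-36 and EQ-5D are to be compared as unadjusted changes from baseline; regression on the baseline already collected would be more precise at almost no cost

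*Protocol article*

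**What the plan says.** All places are in the protocol article.

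- **Baseline and follow-up are both measured.** Outcomes {12}: "RAND SF-36 questionnaires will be filled out preoperatively (baseline) and 6–12 weeks post-surgery". Trial design {8} and the outcome assessment table (Table 2) schedule EQ-5D at the same two points.
- **SF-36 is analysed as change.** Outcomes {12}: "The difference in the change in score to baseline will be compared between the groups".
- **Outcomes in general are treated the same way.** Later in that section: "a comparison will be made between the two groups considering the change to baseline". EQ-5D has no analysis sentence of its own, so its change-score analysis rests on this general statement.
- **EQ-5D also has an exploratory economic use.** "the use of EQ-5D-3L to calculate QALYs at 6–12 weeks postoperative will be explored".
- **Only unadjusted tests are named.** Statistical methods {20a}: "Secondary endpoints will be calculated using a simple" t test, with Mann–Whitney U for non-normal data and Fisher's exact or chi-squared tests as the other options.
- **Adjustment is ruled out.** Methods for additional analyses {20b}: "We do not intend to perform adjusted analyses".

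**The concern.** When a continuous outcome is measured before and after treatment in a randomized trial, the change score is one way to use the baseline. It subtracts the whole baseline value, which amounts to fixing the regression slope of follow-up on baseline at 1. If the true slope is smaller, part of what is subtracted is noise. Regression on the baseline estimates the slope and avoids that loss.

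The choice is not left open here. The article states the change-score comparison, names only unadjusted tests and says that no adjusted analyses are intended. At stake is the precision of the quality-of-life comparisons, and how well the estimates withstand a chance difference in baseline scores between the arms.

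**Working it through.** **Inputs.** The evaluable sample is 167 per arm (Sample size {14}); I assume that all 167 have both questionnaires. The document gives no SD, correlation or power for SF-36 or EQ-5D. The correlation r is therefore assumed over 0.3 to 0.9, and results are in SD units.

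**The plan's own figure.** The only stated calculation is for the primary endpoint, a "non-inferiority trial with a binary outcome using a one-sided alpha of 0.05 and 80% power", with success rates of 93.7% and 95% and a margin of 0.05:

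n per arm = (0.937×0.063 + 0.95×0.05) × (1.645 + 0.842)² / (0.013 + 0.05)² = 165.9, so 166.

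This agrees with the stated 167 within rounding. It does not involve the quality-of-life scores, so nothing below alters it.

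**Variance of the two analyses.** Let s be the SD at both time points (assumed equal). The per-patient variances are:

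- change score: 2(1−r)s²
- ANCOVA: (1−r²)s²
- ratio ANCOVA/change: (1+r)/2

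The confidence interval narrows by 1 − √ratio. The detectable difference with 80% power at two-sided 0.05 is (1.960 + 0.842) × √(2V/167), where V is the per-patient variance. The last column gives the ANCOVA power for an effect that has 80% power under the change-score t test.

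| r (assumed) | Variance ratio | CI narrower by | Detectable, change | Detectable, ANCOVA | ANCOVA power |
|---|---|---|---|---|---|
| 0.3 | 0.65 | 19% | 0.363 SD | 0.292 SD | 93.5% |
| 0.5 | 0.75 | 13% | 0.307 SD | 0.266 SD | 89.9% |
| 0.7 | 0.85 | 8% | 0.237 SD | 0.219 SD | 86.0% |
| 0.9 | 0.95 | 2.5% | 0.137 SD | 0.134 SD | 82.0% |

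At r = 0.5, ANCOVA with 126 per arm (167 × 0.75, rounded up) matches the change-score analysis with 167. Simulation of 4,000 trials for each of r = 0.3, 0.5 and 0.7 gave variance ratios of 0.68, 0.74 and 0.86, with no bias in the ANCOVA estimate.

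**Without the equal-SD assumption.** Let k = follow-up SD / baseline SD, and express variances in units of the baseline variance. The change score has 1 + k² − 2rk and ANCOVA has k²(1−r²). The difference is (1 − rk)², which is never negative and is zero when the slope rk equals 1. So, apart from the one degree of freedom spent on the slope, ANCOVA does not lose. How much it gains depends on how far the slope lies from 1.

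**Chance imbalance.** The difference in baseline means between arms has SD s√(2/167) = 0.109s, so 95% of trials fall within about ±0.21s. Given a baseline difference D, the expected change-score estimate is shifted by −(1−r)D. At r = 0.5 and D = 0.21s the shift is about 0.11s in size, against a detectable difference of 0.307s. Regression on the baseline removes it.

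**The case against.** The strongest reply is that nothing planned here is invalid: over randomizations the change-score t test is unbiased and keeps its type I error. That stands, and it makes this a recommendation on efficiency. Four narrower replies also stand in part.

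- **Size.** The (1+r)/2 ratio needs equal SDs, and r is unknown. At r = 0.9 the gain is only 2.5% in interval width.
- **Mann–Whitney.** If non-normality leads to the rank test, the ratio does not describe the analysis actually run.
- **EQ-5D and QALYs.** The change-score wording is explicit only for SF-36. A QALY is not a change score, so the ratio does not apply to it.
- **Placement.** The sentence ruling out adjustment follows the subgroup list. Read alone, its reach could be disputed, but the section on statistical methods offers only unadjusted tests, so the reading holds for SF-36.

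A reader might infer three stronger points that the document does not support.

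- **That the quality-of-life results will be biased.** The shift shown above is conditional on an observed imbalance and averages to zero over randomizations.
- **That simple randomization, without blocks or strata, makes imbalance in baseline scores likelier.** Blocking controls arm sizes. The spread of the baseline difference stays at about 0.11 SD unless one stratifies on the score itself.
- **That the primary result or the cost-effectiveness claim is compromised.** The QALY work is exploratory, and the economic analysis may turn out to be cost minimization. For the primary endpoint, take the article's leak rates of 2.9% and 5.8% and an assumed 30% infratentorial share. Chance imbalance in approach then has SD √(0.3×0.7×2/175) = 4.9 percentage points. Multiplied by the 2.9-point difference in leak rate, this moves the risk difference by about 0.14 points, which is negligible against a 5-point margin.

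**Conclusion.** The point holds as a low-priority improvement. The article commits to unadjusted change scores for SF-36 and, by its general sentence, for EQ-5D, although both baselines are available for adjustment. With equal SDs and r between 0.3 and 0.9, ANCOVA reduces the variance by 35% to 5% and narrows the confidence intervals by 19% to 2.5%. The direction of the gain does not depend on the assumed values, except that it disappears if the regression slope equals 1; its size cannot be fixed from the document. The effect is limited to secondary and exploratory quality-of-life outcomes. The primary endpoint, the margin and the 334 evaluable or 350 enrolled patients are untouched.

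**What to change.** In the protocol or the SAP, state that SF-36 domain scores and EQ-5D utility at FU3 will be compared by linear regression on treatment arm with the corresponding baseline score as covariate, and that the adjusted mean difference will be reported with its 95% confidence interval. Unadjusted change, or a rank test where the data are clearly non-normal, can remain as a sensitivity analysis. If QALYs are calculated, adjust them for baseline utility. Narrow the sentence in Methods for additional analyses {20b} so that it no longer excludes these models.

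The cost is a few lines of text and one degree of freedom out of about 330. No new data or patients are needed. The blinding section says that allocation is released only after the analysis, so the change can still be specified credibly if it is made before that release.

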### Methods in analysis to handle protocol non-adherence and any statistical methods to handle missing data {20c}

The results will be analyzed according to the “intention-to-treat” (all randomized participants, irrespective of protocol adherence), “per-protocol” (only participants that were treated according to the protocol), and “as-treated” (all participants according to the treatment they received) principles. These three analyses will be compared to show the possible impact of a lack of data on the results. For the primary endpoint, no missing data are expected. For secondary endpoints (cost-effectiveness evaluation), the predictive mean of the other values within the arm will be used.

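### The non-inferiority hypothesis is analysed on three sets with no deciding set and no rule of agreement, so one trial can both pass and fail

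*Protocol article*

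**What the plan says.** Section {14} (Sample size) sets one confirmatory hypothesis on the difference in success rates, L-PRF minus control: "The non-inferiority limit was set at 0.05", and "This is a non-inferiority trial with a binary outcome using a one-sided alpha of 0.05 and 80% power". Success means no clinically relevant CSF leak by 12 weeks. Section {14} also expects departures from allocation: "A drop-out rate of 2–5% is expected due to loss of follow-up and non-adherence to the allocation or failure of L-PRF preparation".

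Section {20c} is the only place that defines analysis sets. It lists ITT (everyone randomized), per-protocol (those treated as the protocol requires) and as-treated (grouped by treatment received). It then states one use for them: "These three analyses will be compared to show the possible impact of a lack of data on the results". It adds that the primary endpoint should have no missing data.

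Two other sections bear on this. Section {11b} lets patients be excluded after allocation, for example when L-PRF preparation fails or intraoperative findings preclude the study procedure. Section {20a} reports the primary difference with a two-sided 95% interval and does not say which limit is compared with −0.05.

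**The concern.** The hypothesis needs a yes or no, but {20c} produces three answers and no way of choosing between them. The purpose it gives does not fill the gap. The three sets differ by adherence to allocation, not by missing data, and the same section expects none missing for this endpoint.

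In a non-inferiority trial the choice of set is not neutral. Crossover can pull the ITT difference towards zero. Per-protocol and as-treated lose the protection of randomization and can also favour L-PRF. Take a patient allocated to L-PRF, closed with sealant, who then leaks. Per-protocol removes that leak from the L-PRF arm, and as-treated moves it to the control arm. With about 20 leaks expected in the whole trial, two such patients can change the result. If the sets split, nothing in the article says which one is the trial's conclusion.

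**Working it through.** **Inputs (section {14}).** "The assumed success rate is 93.7% in the control arm"; for L-PRF, "we assume a 95% success rate based on a prior feasibility study"; margin 0.05; one-sided alpha 0.05; 80% power; 167 per arm, raised to 175.

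**1. The plan's own sample size.** With unpooled variance,
n per arm = [0.937×0.063 + 0.95×0.05] × (1.645 + 0.842)² / (0.95 − 0.937 + 0.05)² = 0.10653 × 6.183 / 0.003969 = 165.9.
That gives 166 per arm. With the multiplier rounded to 6.2 it is 166.4, so 167 per arm and 334 in total, as stated. At one-sided 0.025 the same formula gives 211 per arm (422), so the stated size rests on one-sided 0.05.

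**2. Expected leaks.** 175×0.063 + 175×0.05 = 11.0 + 8.75, about 20.

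**3. One trial, three answers.** This is a constructed example: 12 leaks in 175 (L-PRF) against 10 in 175 (control), with 9 L-PRF patients closed with sealant, 2 of whom leaked. Lower limit = difference in success − z × √[p₁(1−p₁)/n₁ + p₀(1−p₀)/n₀].

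| Set | Leaks, L-PRF v control | Difference in success | SE | Limit, z=1.645 | Limit, z=1.96 |
|---|---|---|---|---|---|
| ITT | 12/175 v 10/175 | −0.0114 | 0.0259 | −0.054 fails | −0.062 fails |
| Per-protocol | 10/166 v 10/175 | −0.0031 | 0.0255 | −0.045 passes | −0.053 fails |
| As-treated | 10/166 v 12/184 | +0.0050 | 0.0259 | −0.038 passes | −0.046 passes |

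The sets split at either confidence level, although at 1.96 only as-treated passes.

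**4. How often this happens.** Simulation: 400,000 trials per scenario, 175 per arm, Wald lower limit against −0.05, all three sets computed on the same trial. Crossover is 2% (4 patients) or 5% (9 patients) of the L-PRF arm, closed with sealant. Random means that they carry the same leak risk as the rest of their arm. The null puts the leak risks at the margin, 6.3% v 11.3%.

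| Quantity, 2% to 5% random crossover | One-sided 5% | 95% interval limit |
|---|---|---|
| False non-inferiority, ITT alone | about 5.5% | about 2.8% |
| False non-inferiority, any of the three | 6.9% to 7.8% | about 3.6% to 4.1% |
| Sets disagree, design rates | about 4% to 7% | 5% to 9% |
| Power, ITT alone | 82% | about 73% |
| Power, ITT and per-protocol both | 81% to 80% | 71% to 69% |

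The excess of ITT alone over its nominal level is small-sample error of the Wald limit, not multiplicity.

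**5. Sensitivity.** In a second simulation, 2–5% in both arms crossed over and took on the risk of the treatment received. Any-of-three error was 7.0–8.8% at one-sided 5%, and disagreement under the design rates was 5–9%. In the step 4 simulation with 5% crossover, an assumed deviator leak risk of 20% or 30% raises any-of-three error to 11.7% or 18.9%. Requiring both ITT and per-protocol keeps it at 5.1% and 5.3%. The formula for three independent tests (1 − 0.95³ = 14.3%) does not apply, because the sets overlap almost completely.

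**The case against.** **No rule says that any one set suffices.** A reader might infer that the trial's error rate exceeds its stated 5%. The article does not support that. It presents the three analyses as a comparison, and reporting all three makes a disagreement visible. If ITT decides, or ITT and per-protocol must agree, there is no multiplicity inflation. This stands: the error figures are conditional.

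**Section {20a} reports a 95% interval.** If its lower limit is the bound, random crossover keeps even the any-of-three error below 5%. This also stands, although that error is still above the nominal 2.5% and the sets still disagree.

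**The large figures are assumed.** Nothing in the article gives a leak risk of 20% or 30% for L-PRF patients closed with sealant. The 17.2% in {14} is for closure without sealant. The expected 2–5% also covers loss to follow-up and is not confined to one arm. So 12–19% is hypothetical. That deviators may be at higher risk is plausible, since {11b} gives an exceptionally damaged dura as its example, but the size is unknown.

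**A condensed article may leave the deciding set to the full protocol or SAP.** It may. But {20c} is not silent. It commits the hypothesis to three sets and assigns them a purpose that does not match how they differ. Nor can the reader assume that ITT decides: {14} treats non-adherence and failed preparation as drop-out, and {11b} allows exclusion after allocation, which sits badly with an ITT set of everyone randomized.

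**Conclusion.** The point holds in limited form. The plan names no deciding set and requires no agreement, so the same data can pass and fail, and the conclusion is open to choice once results are known. The sets disagree in about 4–7% of trials under the design rates at one-sided 5%, assuming 2–5% random crossover from L-PRF to sealant, and more often if crossover is related to leak risk.

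Error inflation is conditional. It arises only if success on any one set is accepted, and with random crossover it is modest: about 7–8% against about 5.5% for ITT alone, or about 3.6–4.1% against a nominal 2.5% at the 95% limit. The change should be made before allocation is released for analysis. Withholding allocation until the analysis is done, as {17} plans, does not settle which result counts.

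**What to change.** Add to {20c}:

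> Non-inferiority is concluded only if the lower confidence limit for the difference in success rate (L-PRF minus control), at the one level stated consistently in {14} and {20a}, exceeds −0.05 in both the intention-to-treat set (all randomized, including patients meeting perioperative exclusion criteria) and the per-protocol set. The as-treated analysis is supportive only.

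Naming one deciding set would also remove the ambiguity. Requiring both is the more cautious choice, and in the scenarios of step 4 at 5% crossover it holds the error at 4.7–5.3% at one-sided 5%.

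The cost is one sentence. It needs no extra visits or measurements, provided that the primary outcome is also collected for patients excluded perioperatively. Power falls by about 1–2 points at one-sided 5%, from 82% to about 80–81%. If the 95% limit is chosen, power is about 73% for ITT alone and 69–71% for both sets, and the power statement in {14} should be restated.

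### Comparing the ITT, per-protocol and as-treated results cannot show the effect of missing leak outcomes, and the premise that none will be missing sits badly with the planned allowance for loss to follow-up

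*Protocol article*

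**What the plan says.** All places are in the protocol article.

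- **Section {20c}** (non-adherence and missing data): "For the primary endpoint, no missing data are expected". An imputation rule follows only for secondary endpoints, with cost-effectiveness named. The primary result is to be analysed by intention to treat (everyone randomized), per protocol and as treated, and "These three analyses will be compared to show the possible impact of a lack of data on the results".
- **Sample size {14}**: "A drop-out rate of 2–5% is expected due to loss of follow-up". The sentence goes on to name two further causes, not keeping to the allocated treatment and failed L-PRF preparation. The sample is raised from 334 to 350 for all three together.
- **Section {11b}**: withdrawal ends all later data collection, and patients may be excluded after allocation for intraoperative reasons.
- **Section {18b}**: a patient who misses the 6–12 week visit and cannot be reached by telephone for the questionnaires counts as lost.
- **Outcomes {12}**: the endpoint is freedom from a clinically relevant leak at 12 weeks. Complications are taken from hospital databases.

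**The concern.** Two statements need attention.

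First, the premise. The plan budgets for patients lost to follow-up and stops data collection at withdrawal, yet expects every 12-week leak status to be known. After discharge there is one scheduled visit, between 6 and 12 weeks.

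Second, the check. The plan names a three-way comparison as its way of showing what a lack of data does to the result. That comparison varies who counts as adherent and which treatment label applies. It does not vary what is assumed about an unknown outcome. The report could therefore state that the result is robust to missing data when this was never examined.

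The direction matters in a non-inferiority trial: leaks that go unseen in the L-PRF arm favour passing. With about 20 leaks expected in total, a handful can decide a borderline result.

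**Working it through.** **Why the check cannot work.** Take a patient whose leak status at 12 weeks is unknown:

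| Patient | ITT | Per-protocol | As-treated |
|---|---|---|---|
| L-PRF as allocated, then lost | L-PRF arm, unknown | L-PRF arm, unknown | L-PRF arm, unknown |
| Sealant as allocated, then lost | Control arm, unknown | Control arm, unknown | Control arm, unknown |

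Whether an unknown is left out or counted as a success, the same is done in all three columns. The three results can agree and share the same bias.

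**Inputs (Sample size {14}, Trial design {8}).** "using a one-sided alpha of 0.05 and 80% power"; "The assumed success rate is 93.7% in the control arm"; "we assume a 95% success rate based on a prior feasibility study"; margin 0.05 absolute; 1:1 allocation.

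**The plan's own figure.** n per arm = (1.645 + 0.842)² × (0.95×0.05 + 0.937×0.063) / (0.95 − 0.937 + 0.05)² = 6.18 × 0.1065 / 0.00397 ≈ 166, so 332 in total against the stated 334. It reproduces. For drop-out, 334/0.98 = 341 and 334/0.95 = 352. Enrolling 350 leaves room for 16 losses (4.6%).

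**Ceiling on missing outcomes.** 2% of 350 = 7 and 5% of 350 = 17.5, so 7 to 18 patients, or about 3.5 to 9 per arm if evenly split. Expected leaks: 175×0.063 + 175×0.05 = 11.0 + 8.75 ≈ 20.

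**Tipping points.** Upper limit for excess leaks = (pL − pC) + z × √[pL(1−pL)/nL + pC(1−pC)/nC], a pass if below 5 points. I use z = 1.645 (90% interval, matching one-sided 0.05) and z = 1.96 (the two-sided 95% interval that section {20a} reports). Counts are L-PRF v control.

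| Data | 90% limit | 95% limit |
|---|---|---|
| *Start A: 8/166 v 10/166 observed, 9 missing per arm* | 2.9 pass | 3.7 pass |
| 3 missing L-PRF leak, 0 control: 11/175 v 10/175 | 4.7 pass | 5.5 fail |
| 3 missing L-PRF leak, 1 control: 11/175 v 11/175 | 4.3 pass | 5.1 fail |
| 4 missing L-PRF leak, 0 control: 12/175 v 10/175 | 5.4 fail | 6.2 fail |
| 4 missing L-PRF leak, 1 control: 12/175 v 11/175 | 4.9 pass | 5.8 fail |
| *Start B: 9 v 11 leaks (planning rates), no unseen leaks: 9/175 v 11/175* | 2.9 pass | 3.7 pass |
| 2 unseen L-PRF leaks: 11/175 v 11/175 | 4.3 pass | 5.1 fail |
| 4 unseen L-PRF leaks: 13/175 v 11/175 | 5.6 fail | 6.4 fail |

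The result therefore turns at 2 to 3 unseen L-PRF leaks on the 95% interval and at 4 on the 90% interval (3 by Newcombe's method from start B), with no leak among missing controls.

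**Error rate at the margin.** True leak rates are 11.3% v 6.3%. If a fraction m is missing and leak patients are three times as likely to be missing, then q = m/(1 + 2p) for non-leak patients, and the observed leak rate is p(1 − 3q)/(1 − m). At m = 5% this gives 10.4% and 5.7%; at m = 2% it gives 11.0% and 6.1%. Exact binomial probability of a pass at one-sided 0.05:

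| Missing | Observed per arm | Unrelated to leak | Threefold, both arms | Threefold, L-PRF only |
|---|---|---|---|---|
| 2% | 171 | 5.3% | 5.8% | 6.6% |
| 5% | 166 | 5.5% | 6.9% | 9.4% |

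On the 95% interval with 5% missing, the three figures are 2.9%, 3.7% and 5.3%.

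**The case against.** The case on the other side limits the size considerably.

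- **The 2–5% is pooled.** Two of its three causes, non-adherence and failed preparation, need not remove the leak outcome. A reader might take 7 to 18 as the plan's forecast of missing primary outcomes. It is only a ceiling.
- **Expecting complete data has a basis.** A leak that needs revision, puncture, a longer stay or repeat imaging leaves a hospital record, and two of the three follow-up assessments are in hospital. Being lost under section {18b} turns on an unanswered call about questionnaires, so leak status may still be recoverable. This stands, except after withdrawal and for care sought elsewhere. A reader might call the two sections flatly contradictory; optimistic is the fairer word.
- **No complete-case rule is written.** A reader might infer one, but section {20c} only says that ITT covers everyone randomized.
- **The comparison is not empty.** Patients excluded after allocation, if still followed, are in ITT but not per protocol, so it shows the effect of setting them aside. This stands, but it concerns non-adherence.
- **The flips are corner cases.** The four-leak flip from start A needs 4 of 9 missing L-PRF patients to leak. That has probability 0.0006 at a 5% leak rate and 0.034 at 15%. One control leak among the missing restores the pass on the 90% interval (though three L-PRF leaks and one control leak still just fail on the 95% interval).
- **Detailed missing-data methods belong in an SAP.** That is right for the method, but the no-missing premise and the unsuitable check are both stated in the article.

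**Conclusion.** The stated check does not do its stated job. This is a wrong rule in the text, not an omitted detail. The no-missing-data statement is optimistic given the allowance for loss to follow-up and the stop at withdrawal.

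The practical effect is modest. Loss that is random and equal between arms leaves the error near 5.3–5.5%. Harm requires loss related to leaking, chiefly in the L-PRF arm. The error figures rest on an assumed factor of three and on 2–5% truly missing, which is the upper end of what the article supports. The flips rest on a borderline result, on 175 patients per arm and on no leaks among missing controls.

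A reader might infer that the primary result would be invalid, or that a failed trial would probably pass. The documents support neither. What they support is that a claim of robustness to missing data, based on the three sets, would be unfounded. This should be fixed, but it does not put the design in doubt.

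**What to change.** In section {20c}:

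1. Delete the statement that no primary-endpoint data are expected to be missing.
2. Describe the comparison of the three analysis sets as a check on non-adherence only.
3. Prespecify, for the ITT primary analysis, a tipping-point table over the number of leaks among patients with unknown 12-week leak status in each arm. Include the worst case (every missing L-PRF patient a leak, every missing control leak-free) and report the table beside the primary interval.

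The choice of imputation method, if any, can be left to the SAP; with about 20 expected leaks it is open to debate. The cost is a few lines of text and one table. With up to 9 missing per arm, the table has at most 10 × 10 = 100 cells. No extra patients or visits are needed. The drawback is that the conclusion may read as less certain.
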